## Abstract

**Background:**

Patients with uncontrolled asthma despite the use of inhaled corticosteroids (ICS), may have a variety of biological pathways driving their airway inflammation. Londamocitinib (AZD4604), a selective, inhaled, Janus kinase 1 inhibitor, has been designed to target a broad inflammatory cytokine profile including those classically unresponsive to ICS. The ARTEMISIA mechanistic study aims to provide a clear understanding of the pathways impacted by londamocitinib in the lung, determine how this impact is reflected in the nose and periphery, and identify candidate biomarkers of londamocitinib-treatment response in asthma. This article reports the design and objectives of the ARTEMISIA study.

**Methods:**

ARTEMISIA is a placebo-controlled, double-blind study of adults with moderate-to-severe asthma aiming to assess the effects of inhaled londamocitinib on Type 2 (T2) and non-T2 driven inflammatory pathways. Extensive parallel bio-sampling of the lung target tissue, nasal mucosa, blood and urine will be performed prior to the first dose and after 4-weeks of treatment with either londamocitinib or placebo. The main objectives of the study are to evaluate the effect of londamocitinib on gene expression in endobronchial brushings and signal transducer and activator of transcription (STAT) phosphorylation in endobronchial biopsies. Key exploratory objectives include investigating the correlation between inflammatory phenotype-specific bronchial epithelial gene signatures and other biomarkers in the lung and peripheral samples; as well as analysis of transcriptomic, proteomic, and metabolomic biomarkers in the nose, blood, and urine.

**Discussion:**

ARTEMISIA commenced recruitment in 2024 and is poised to deliver a deep understanding of the mechanism of action of londamocitinib and its potential to impact on a population of asthmatics with high unmet need. The multiomic analysis of paired central and peripheral samples may reveal novel insights into the connection and translation between these compartments, deepen understanding of airways disease, and identify novel candidate biomarkers for asthma and JAK activity. In addition to sampling the airway directly, with parallel nasal and peripheral bio-sampling mirrored by the Phase 2a AJAX study (NCT06020014), the ARTEMISIA study may provide a unique link between bronchial assessed mechanisms of action and clinical outcomes.

**Trial registration:**

NCT06435273 (ClinicalTrials.gov). Registered 24th May 2024.

## Background

Asthma is a chronic respiratory disease typified by variable symptoms and airflow limitation related to complex underlying airways inflammation [1]. Whilst for several decades the mainstay of treatment for asthma has been inhaled corticosteroids (ICS) with or without long-acting beta agonists (LABA), the emergence of targeted biologic therapies has driven a new wave of asthma phenotyping and a deeper understanding of its pathobiology. Most current biologic approaches are directed to T2-high cytokine (e.g. Interleukins [IL] 4, 5, and 13) and epithelial alarmin (e.g. thymic stromal lymphopoietin [TSLP], IL-33) based mechanisms which overlap significantly with those pathways that are corticosteroid sensitive [2]. In fact, many clinical trials of these agents have been specifically directed to those patients whose only option has been systemic corticosteroids [3]. However, it is becoming increasingly apparent that many individuals with asthma have at least a component of co-existing non-T2, corticosteroid insensitive airways inflammation (e.g. IL-6, IL-17 and neutrophilic) that continues to drive poor asthma control even after all currently available approaches have been exhausted [4]. There is an urgent need to develop new therapies that target inflammation beyond the classic, predominantly T2 phenotype [1].

Londamocitinib (AZD4604) is a highly selective Janus kinase 1 (JAK1) inhibitor that is being developed as a novel inhaled therapy in patients with uncontrolled asthma despite ICS use [5–7]. It exhibits broad inhibition of signalling induced by JAK1-dependent cytokines associated with the entire spectrum of inflammatory phenotypes observed in asthma (Fig. 1) [6]. Because of this, inhaled londamocitinib is expected to impact on inflammatory mechanisms that are both responsive and resistant to corticosteroids, whilst minimising the potential systemic adverse effects associated with non-selective, oral JAK inhibitors [7].

**Fig. 1 Fig1:**
[figure not shown]
Proposed mechanism of action of londamocitinib. Janus kinase 1 inhibition reduces STAT1/3/5/6 phosphorylation, suppressing inflammatory pathways relevant in asthma, with broader effects than single cytokine biologics. Londamocitinib, a selective JAK1 inhibitor, therefore, has the potential to benefit patients with asthma, including those with steroid-insensitive inflammation, by targeting T2 and non-T2 airway pathology. IFN: Interferon; IL: Interleukin; JAK1: Janus kinase 1; pSTAT: phosphorylated signal transducer and activator of transcription; T2: Type 2; Th: T-helper; TSLP: thymic stromal lymphopoietin. Created with BioRender.com

A phase 2a clinical trial (AJAX, NCT06020014 [ClinicalTrials.gov], registration date 25th August 2023) is currently in progress assessing the clinical efficacy of londamocitinib in a broad population of patients with moderate-to-severe asthma. In parallel with this study, the ARTEMISIA (**A**i**R**way **T**arget **E**ngagement and **M**echanistic **I**nsight**S** of Janus kinase **I**nhibition in **A**sthma) study (NCT06435273) has been designed to obtain a deeper understanding of the mechanism of action of londamocitinib, evaluate the impact upon asthma-related pathways it may inhibit, and holds the potential to identify putative precision medicine biomarkers to guide asthma therapy [8]. In addition to sampling the airway directly, the ARTEMISIA study includes a parallel nasal and peripheral bio-sampling strategy that is shared with the AJAX study, providing a unique link between bronchial assessed mechanisms and clinical outcomes.

## Methods/design

### Study design

ARTEMISIA is a randomised, double-blind, placebo-controlled, parallel-group, exploratory, phase 2 study (NCT06435273). It aims to assess the effect of londamocitinib, administered twice daily via dry-powder inhalation for four weeks, on the wide spectrum of inflammatory signalling pathways that drive pathology in adults with moderate-to-severe asthma. The ARTEMISIA study is currently ongoing across 5 countries (Canada, Denmark, Germany, Spain, and the United Kingdom [UK]) and aims to enrol 48 participants, randomised 2:1 to londamocitinib or placebo respectively (see Fig. 2). Participants will be stratified based on fractional exhaled nitric oxide (FeNO) (≥ or < 25 parts per billion [ppb]); with at least 40% of randomised participants with FeNO ≥ 25 ppb and at least 40% with FeNO < 25 ppb at baseline.

**Fig. 2 Fig2:**
[figure not shown]
ARTEMISIA study design. Figure to illustrate the design of the ARTEMISIA study. Bronchoscopies will be undertaken to take endobronchial brushings and biopsies. Nasal sampling will consist of nasal lining fluid (nasosorption) and nasal cell (curettage) sampling. Peripheral sampling will consist of venous blood and urine. ACQ: Asthma Control Questionnaire; BID: Twice daily; CAAT: Chronic Airways Assessment Test; FeNO: Fractional exhaled nitric oxide

### Inclusion criteria and recruitment

Participants eligible for the study will be aged 18–75 years and be receiving medium- or high-dose ICS and LABA with or without additional controller medication (e.g. leukotriene receptor antagonist or long-acting muscarinic antagonist) for at least 2 months prior to Visit 1 (screening) and have a history of either at least one severe asthma exacerbation within the year prior to Visit 1 or an asthma control questionnaire 6 (ACQ-6) score ≥ 1.5 during screening and prior to randomisation. Asthma patients using maintenance oral corticosteroids, systemic biologics, or ICS + fast-acting β2 agonist as a rescue medication (maintenance and reliever therapy or anti-inflammatory reliever therapy) are not eligible for the study. Key inclusion and exclusion criteria are summarised in Table 1. For the duration of the study, participants will continue to use their asthma maintenance therapy as prescribed, without change. Participants are also allowed to use short-acting β_2_ agonists as rescue medication.

**Table 1 Tab1:** Key inclusion and exclusion criteria for ARTEMISIA

**Key inclusion criteria**
• Male or female, aged 18–75 years
• Body weight ≥ 40 kg and body mass index < 35 kg/m^2^
• Documented physician-diagnosed asthma for ≥ 12 months prior to visit 1
• Physician-prescribed asthma controller medication with medium- or high-dose ICS for ≥ 2 months before visit 1 (as per GINA 2023 guidelines) [9]
• Predicted normal morning pre-bronchodilator FEV_1_ ≥ 60% at visit 1 and visit 3a
• Documented evidence of asthma in previous 5 years prior to visit 1 or during screening.
• Either a history of a severe asthma exacerbation within the year prior to visit 1 or an ACQ-6 score ≥ 1.5 at Visit 1 and Visit 3a
**Key exclusion criteria**
• Clinically important pulmonary disease other than asthma
• A severe asthma exacerbation within 8 weeks prior to Visit 1
• Any disorder or major physical impairment that is not stable in the opinion of the investigator and could affect the safety of the participant throughout the study
• Any clinically significant cardiac or cerebrovascular disease
• History of venous thromboembolism, malignancy, or HIV infection
• Evidence of infective hepatitis
• Current smokers or patients with a smoking history of ≥ 10 pack-years
• Treatment with marketed biologics within 6 months or 5 half-lives of Visit 1
• Treatment with ICS plus fast-acting β2 agonist as a rescue medication (e.g., Maintenance and Reliever Treatment) is not allowed 30 days prior to Visit 1.
• Treatment with systemic corticosteroid (short-term or maintenance) use within 8 weeks (oral) or 12 weeks (intramuscular) before Visit 1.

Table detailing the key inclusion and exclusion criteria for the ARTEMISIA study. ACQ: Asthma Control Questionnaire; FEV_1_: GINA: Global Initiative for Asthma; HIV: Human immunodeficiency virus; ICS: Inhaled corticosteroids

The study consists of a screening period, 3-week run-in and baseline period, 4-week treatment period, and 1-week follow-up period (see Fig. 2).

### Objectives and outcome measures

**Table 2 Tab2:** Objectives and endpoints for ARTEMISIA

Objective	Endpoint(s)
**Primary objective**	
Evaluate the effect of londamocitinib compared to placebo on gene expression in airway epithelial cells	Change from baseline to end of treatment in expression of T2, non-T2, and JAK1-related genes and gene signatures in bronchial brushings
**Secondary objectives**	
Evaluate the effect of londamocitinib compared to placebo on STAT phosphorylation in the airways	Change from baseline to end of study drug administration in STAT phosphorylation in bronchial biopsies
Explore the effect of londamocitinib on cellular pathology in the airways compared to placebo	Change in number of airway cells, including but not limited to inflammatory cells, airway smooth muscle cells, and goblet cells from baseline to end of treatment in bronchial biopsies (cells per mm² determined by microscopic evaluation)
**Key Exploratory Objectives**	
Explore if the specific inflammatory phenotypes (e.g., T2 and non-T2) in the lung are reflected in the nose and blood	Correlation of inflammatory phenotype-specific bronchial epithelial gene signatures and biomarkers with signatures and biomarkers from peripheral samples (including but not limited to blood and nasal samples)
Explore the effect of londamocitinib on biomarkers of inflammation and asthma, investigate biomarkers for predicting response to londamocitinib, evaluate exploratory biomarkers in asthma, and evaluate systemic impact on peripheral samples	The change from baseline to end of treatment in exploratory biomarkers

Table detailing the primary, secondary and key exploratory endpoints for the ARTEMISIA study. JAK: Janus kinase; STAT: signal transducer and activator of transcription; T2: type-2

The primary, secondary and key exploratory objectives and endpoints for this study are listed in Table 2. The primary objective of the ARTEMISIA study is to explore the effect of londamocitinib as compared to placebo on gene expression in airway epithelial cells. This will be assessed as a change from baseline to 4-weeks of treatment in expression of T2, non-T2, and JAK1-related genes and gene signatures in bronchial brushings. A secondary objective is to evaluate the effect of londamocitinib as compared to placebo on STAT phosphorylation in the airways. This will be assessed as change from baseline to 4-weeks of treatment in STAT phosphorylation in endobronchial biopsies. An additional secondary objective is to explore the effect of londamocitinib on cellular pathology in the airways as compared to placebo, assessed as change in number of airway cells, including but not limited to inflammatory cells, airway smooth muscle cells, and goblet cells.

One of our key exploratory objectives is to examine the effect of londamocitinib on biomarkers of inflammation and asthma, in order to identify biomarkers associated with a response to londamocitinib, evaluate exploratory biomarkers in asthma, and evaluate systemic impact on peripheral samples. This work will enable us to identify patterns linking changes in the central airways to tractable molecular biomarkers in peripheral samples, and subsequently combine this data with that obtained from the AJAX study to explore how these potential biomarkers relate to clinical outcomes (see Fig. 3).

**Fig. 3 Fig3:**
[figure not shown]
ARTEMISIA and AJAX data will be combined to relate lung sample findings with clinical outcomes. The AJAX and ARTEMISIA studies are being performed in parallel to facilitate the development of londamocitinib for moderate-severe asthma. BID: Twice daily; CompEx Asthma - Composite endpoint for asthma exacerbations [10]. Created with BioRender.com

### Biospecimen collection and analysis plan

Paired lung, nasal, and peripheral samples will be collected prior to the first dose at Visit 3a and again at the end of the treatment period at Visit 6a (Figs. 2 and 4). Whole blood, serum, and plasma will be collected, processed per standard protocols, and stored for exploratory transcriptomics and proteomics analysis. Urine will be collected and immediately frozen without additives for exploratory metabolomics analysis. Nasal mucosal lining fluid will be collected via nasosorption from each nostril and stored for exploratory proteomics analysis. Nasal curettage will then be performed for each nostril and cellular material combined into a single tube containing RNAlater solution and cryopreserved for bulk ribonucleic acid (RNA) sequencing at the end of the study.

**Fig. 4 Fig4:**
[figure not shown]
Sampling and biomarker strategy for both the ARTEMISIA and AJAX studies. Molecular biomarkers in more easily accessible matrices, such as nasal samples, blood, and urine will be correlated to T2 and non-T2 bronchial epithelial gene signatures amenable to londamocitinib modulation. Complementary precision sampling in AJAX and ARTEMISIA will enable the exploration of a link between lung airway mechanisms and clinical efficacy to identify biomarkers predictive of a response to londamocitinib and inform patient subgroups in asthma. CompEx Asthma - Composite endpoint for asthma exacerbations [10]; FeNO: Fractional exhaled nitric oxide; IHC – immunohistochemistry; pSTAT– phosphorylated signal transducer and activator of transcription; RNA: Ribonucleic acid; Seq: Sequencing; SNP: Single nucleotide polymorphism; T2: Type-2

Endobronchial brushings and biopsies will be collected via bronchoscopy following local guidelines. The aim will be to collect a total of 6 endobronchial brushings followed by 6 endobronchial biopsies from the 2nd to 5th order carinae of the right lung. All six brushing samples will be collected in a single tube containing RNAlater solution and cryopreserved for bulk RNA sequencing at the end of the study. Four of the biopsies will be fixed in neutral buffered formalin and embedded in paraffin for analysis of cellular pathology and STAT phosphorylation by immunohistochemistry. Two of the biopsies will be immediately snap frozen and stored for proteomics analysis (Fig. 5).

**Fig. 5 Fig5:**
[figure not shown]
Processing of bronchoscopic samples. Highly prescriptive sample acquisition and handling protocols were provided to ensure sample handling was consistent across the sites. Created with BioRender.com

To ensure uniformity of sample acquisition and handling processes, detailed protocols describing these procedures were provided to sites, alongside comprehensive training sessions.

### Biomarker inclusion for primary endpoint

The primary endpoint of ARTEMISIA is designed to assess the proposed broad anti-inflammatory effects of londamocitinib on Th1, Th2, Th17, and IL-6 trans signalling pathways. As such, we have pre-defined genes and gene sets reporting on the different inflammatory pathways, which will be interrogated in the transcriptomic data sets generated from bronchial brushings pre- and post-treatment with londamocitinib or placebo. These genes and gene sets were selected based on integrating in-house data obtained through the *in vitro* treatment of human bronchial epithelial cell lines with relevant cytokine stimuli plus or minus londamocitinib along with published data derived from lung samples from patients with asthma [11–14]. Our analysis plan for the primary endpoint will follow a similar approach used in our previous study, in which the IL-6 trans signalling signature was derived and used to interrogate expression of this pathway in lung brushings from patients with asthma [15].

In brief, our strategy for analysing individual genes will be to consider a 20%-fold change in either direction from baseline to post-treatment to be the minimally interesting effect, depending on what is expected for the individual gene. The average fold change will then be compared between the londamocitinib and placebo arms. For gene signatures, gene set variation analysis (GSVA) and single-sample scoring (singscore) will be used to compare changes between the two treatment arms.

### Statistical considerations

All statistical analyses of primary, secondary and exploratory outcomes will be performed after database lock, which will occur after the last subject last visit study milestone.

Data on patient demographics and disease characteristics, as well as safety findings, will be reported descriptively for the full analysis set (all randomised participants who receive at least one dose of study drug irrespective of protocol adherence and continued participation in the study).

Due to the exploratory nature of the study, no formal power calculation was performed. The sample size of 48 participants was estimated based on a large sample z-statistic around the difference in change from baseline values between londamocitinib and placebo on the logarithmic scale. A pooled standard deviation for change from baseline across T2 genes was derived from a historical bronchoscopy study [13]. Assuming comparable variability, the estimated sample size will ensure that the two-sided 95% confidence intervals for the biomarkers of interest will not be wider than 0.72 on the log-change from baseline scale, which is considered sufficiently narrow for the purposes of this study.

The bulk RNA-sequencing data collected for the primary endpoint will be analysed using negative-binomial regression models designed for count-based gene expression data [16, 17]. Variations in sequencing depth between samples will be modelled, along with adjustment for study drug as a covariate. A natural-logarithm link function will be used for the generalised linear model, but results will be presented in terms of a log-2-fold change. The treatment effect on gene-expression change from baseline will be analysed in a paired fashion.

The secondary endpoints aim to evaluate the effect of londamocitinib compared to placebo on various bronchial biopsy measures throughout the study and will be analysed using analysis of covariance (ANCOVA) models. The within-participant change from baseline to end of treatment measures of STAT phosphorylation and airway inflammatory cells from the bronchial biopsies will be modelled individually on the log-scale and will include baseline value and study drug as covariates.

The exploratory endpoints will further describe biomarker effects and summarise the effect of londamocitinib on lung function and asthma characteristics throughout the study compared to placebo. The analysis of additional biomarker expression values will follow similar methods as in the primary endpoint analysis. Change from baseline spirometry values will be analysed using Mixed Model for Repeated Measures (MMRM) methods. Additional asthma disease characteristics and pharmacokinetic measures will be summarised descriptively and with graphical displays.

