The primary objective of ARTEMISIA is to assess the change in epithelial gene signatures of central airways following 4 weeks of exposure to londamocitinib. Many studies investigating the impact of drugs on the airways have focussed on the histopathological changes seen in the airway [18, 19]. Local effects of blocking IL-13 signalling on eosinophilic airway inflammation in moderate-severe asthmatics was investigated in the MESOS and CLAVIER studies [19, 20]. In these studies, neither tralokinumab nor lebrikizumab treatment resulted in a significant effect on change from baseline in airway submucosal eosinophils versus placebo. It should be noted however that enrolment to the CLAVIER study was stopped before inclusion of the planned number of participants. Inhibition of TSLP signalling in the CASCADE study did result in a significantly greater change from baseline to the end of treatment in airway submucosal eosinophils with tezepelumab compared to placebo (ratio of geometric least-squares means 0·15 [95% CI 0·05–0·41]; nominal *p* < 0·0010) [18]. To adequately assess these changes requires prolonged exposure to the drug and substantial cohorts, leading to large, lengthy studies which can be difficult to recruit to and lead to incomplete datasets [20]. Using gene expression as our primary endpoint allows us to evaluate inflammatory changes whilst reducing both duration of exposure to study drug and sample size for the study. This not only allows us to evaluate mechanism of action in a more efficient way, but also allows us to address the ethical imperative of reducing the number of participants involved in an invasive study, particularly at this early stage of drug development. Whilst the primary objective of the ARTEMISIA study is to assess the change in epithelial gene signatures, the study will also assess the impact of inhibiting the IL-13, IL-4, IL-6, IFN-γ and TSLP signalling pathways on cellular pathology as a secondary objective.

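### The 0.72 confidence-interval width is an expected value for a gene of pooled T2 variability, not a ceiling that 48 participants can ensure for every biomarker of interest

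*Protocol article*

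**What the plan says.** Study design gives the size and allocation: the trial "aims to enrol 48 participants, randomised 2:1 to londamocitinib or placebo respectively", which is 32 and 16.

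Statistical considerations says that no formal power calculation was done because the study is exploratory. The number was instead obtained from a calculation "based on a large sample z-statistic around the difference in change from baseline values between londamocitinib and placebo on the logarithmic scale". The variability input is described thus: "A pooled standard deviation for change from baseline across T2 genes was derived from a historical bronchoscopy study". The conclusion opens with a condition, "Assuming comparable variability, the estimated sample size will ensure", and the claim itself reads: "the estimated sample size will ensure that the two-sided 95% confidence intervals for the biomarkers of interest will not be wider than 0.72", in units of log change. The article regards that width as narrow enough for its purpose.

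The claim covers the "two-sided 95% confidence intervals for the biomarkers of interest". Table 2 defines the primary endpoint as change in T2, non-T2 and JAK1-related genes and signatures in bronchial brushings. The section on biomarkers for the primary endpoint says that genes will also be analysed one by one.

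**The concern.** The wording promises an upper bound, but a width calculated at one fixed SD is not an upper bound, for three reasons.

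- The interval is computed from the SD observed in the trial, which varies around the true value.
- A pooled SD is a kind of average, so some genes in the pool lie above it.
- The pool holds T2 genes only, while the claim is made for all biomarkers of interest.

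At stake is the only quantitative property given for the design. A reader would take it that every gene in the primary endpoint will have an interval of 0.72 or less. Support is thinnest for the non-T2 pathways, which the Discussion names as a purpose of the study.

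**Working it through.** **Inputs.** From the article: 48 participants at 2:1 (32 and 16), two-sided 95% confidence, z quantile 1.960, full width 0.72. The SD is not printed and must be back-solved. The loss rates and the alternative SDs below are assumptions; the article gives none.

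**1. The plan's figure.**

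Full width = 2 × z × SD × √(1/n₁ + 1/n₂)

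- √(1/32 + 1/16) = 0.3062
- 2 × 1.960 × 0.3062 = 1.200, so width = 1.200 × SD with 48 evaluable pairs
- 0.72 / 1.200 gives SD = 0.600

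Forward, SD 0.60 gives 0.7201. The figure is coherent with a planning SD of 0.60 and no loss of pairs. This is not an independent reproduction, because the SD was solved from the answer. Smaller SDs fit fewer pairs: 0.72 is also the computed width at SD 0.581 with 45 pairs, 0.561 with 42, and 0.520 with 36.

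**2. Expected width against ceiling.** Suppose the true SD equals the planning SD and 0.72 is the computed width at the number of pairs analysed. With the z quantile, the observed width exceeds 0.72 whenever the sample SD exceeds the true SD. With 46 degrees of freedom:

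P(χ²₄₆ > 46) = 0.47

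This does not depend on the size of the SD and barely depends on the number of pairs (34 degrees of freedom also gives 0.47). With the t quantile (2.013), the expected width is 0.740 at SD 0.60, and the chance of exceeding 0.72 is P(χ²₄₆ > 46 × (1.960/2.013)²) = 0.57. The change from z to t adds only 2.7% to the width.

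If the plan holds slack, the chance is lower. With SD 0.520 and all 48 pairs, the computed width is 1.200 × 0.520 = 0.624, and P(χ²₄₆ > 46 × (0.72/0.624)²) is about 0.07. That is still not zero.

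**3. Genes above the pooled SD.** Width with 48 pairs and z:

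| SD of the gene (assumed) | Width |
|---|---|
| 0.6 | 0.72 |
| 0.7 | 0.84 |
| 0.8 | 0.96 |
| 0.9 | 1.08 |

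This applies to the more variable T2 genes, and to any non-T2 or JAK1-related gene whose SD is above the pooled T2 value.

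**4. Loss of pairs.** The change from baseline is analysed in pairs, so a participant contributes only with usable brushings at both visits. At SD 0.60 and 2:1:

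| Pairs lost (assumed) | Evaluable pairs | Width, z | Width, t |
|---|---|---|---|
| 0% | 48 | 0.72 | 0.74 |
| 10% | 43.2 | 0.76 | 0.78 |
| 20% | 38.4 | 0.81 | 0.83 |

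**The case against.** The strongest defence is that the sentence is conditional. It assumes variability comparable with the historical study, and the article discloses both the z approximation and the T2 source of the SD. No printed arithmetic is wrong. Any precision calculation at a fixed SD is exceeded about half the time, and the article claims no assurance probability. The primary analysis is a negative-binomial model, so a t interval with 46 degrees of freedom is itself only an approximation. The study is hypothesis-generating, the article concedes that its small size may limit interpretation, and no decision rule rests on 0.72.

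Most of this stands, and it limits the size of the point. It does not rescue the guarantee: comparable variability makes the pooled SD right on average, but it neither fixes the observed SD nor brings every gene down to the pooled value.

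Stronger readings are tempting, and the article does not support them:

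- **That 0.72 requires all 48 pairs, or is not delivered.** The SD is not printed. The round back-solved value makes planning without losses likely, but a smaller SD would leave room for loss.
- **That the article forecasts missing data in this trial.** Its remark "difficult to recruit to and lead to incomplete datasets" concerns large, lengthy studies of histopathological change, to which it presents this shorter gene-expression design as the alternative. It gives no loss rate.
- **That leaving out the SD or an allowance for lost pairs is a defect.** The full protocol or analysis plan may hold both.

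**Conclusion.** The point holds as one about an overstated claim. The figure of 0.72 is an expected width for a gene with the pooled T2 SD under a large-sample approximation. At that SD the observed width would exceed it about half the time (47% with z, 57% with t), provided 0.72 is the computed width at the planned number of pairs. Genes more variable than the pooled SD exceed it in expectation, in proportion to their SD. Whether non-T2 and JAK1-related genes are among them cannot be told from the article, which carries T2 variability over to them without citing a figure.

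The 47% does not need the value of the SD. The widths under loss of pairs rest on the back-solved SD of 0.60 and on assumed loss rates. The consequence is modest in an exploratory study without a power claim, but this is its only stated operating figure, and correcting it is cheap.

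**What to change.** Replace the guarantee in Statistical considerations with a statement of this kind: the expected 95% confidence-interval width is about 0.72 for a gene with the pooled T2 SD at the planned number of evaluable pairs; widths for other genes, including non-T2 and JAK1-related genes, scale with their SD (about 1.2 × SD with 48 evaluable pairs) and widen as pairs are lost.

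The sponsor should insert its own SD, log base and evaluable number; the 0.60 used here is back-solved and should not be printed as a trial input. The base matters because the model uses a natural-log link while results are to be shown as log2 fold changes. If 0.72 is in natural logs, it is 0.72/0.693 = 1.04 on the log2 scale.

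The cost is a slightly less favourable stated figure. No extra participants and no change to the analysis are needed.

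### The primary gene-expression analysis compares changes with no baseline-expression term named; adjusting for baseline, as the secondary endpoints do, would give a modest gain in precision

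*Protocol article*

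**What the plan says.** Under Statistical considerations, the primary RNA-sequencing counts go into negative-binomial regression with a log link. The terms named are sequencing depth and study drug, and the section adds: "The treatment effect on gene-expression change from baseline will be analysed in a paired fashion".

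Biomarker inclusion for primary endpoint describes the contrast for single genes: "The average fold change will then be compared between the londamocitinib and placebo arms". For signatures it says that GSVA and singscore will be used to compare changes between the arms. Neither section names the baseline level of a gene or score as a covariate.

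The secondary endpoints are treated differently. STAT phosphorylation and airway cell counts from the biopsies "will be modelled individually on the log-scale and will include baseline value and study drug as covariates".

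The sample size rests on precision alone: "Due to the exploratory nature of the study, no formal power calculation was performed". It was derived from a "large sample z-statistic around the difference in change from baseline values between londamocitinib and placebo on the logarithmic scale", and is said to ensure that the "two-sided 95% confidence intervals for the biomarkers of interest will not be wider than 0.72 on the log-change from baseline scale". The article regards that width as narrow enough for its purposes. Under Study design, the trial "aims to enrol 48 participants, randomised 2:1 to londamocitinib or placebo respectively", which gives 32 and 16, with randomisation stratified by FeNO.

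**The concern.** Comparing changes amounts to subtracting the baseline with a fixed coefficient of 1. When baseline and end-of-treatment values correlate imperfectly, that is too large a coefficient. Part of a chance baseline difference between arms then returns in the estimate as regression to the mean, and the interval is wider than it need be. ANCOVA estimates the coefficient from the data instead.

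The article adopts ANCOVA for its secondary endpoints but names no such term for the primary one, where interval width is the only sample-size justification. At stake is precision on the primary endpoint that could be had from samples already collected, with only 16 placebo participants and two bronchoscopies per participant.

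**Working it through.** **Inputs.** N = 48 at 2:1, so 32 and 16 (Study design). Two-sided 95% interval, width at most 0.72, z-based, for the difference in log change from baseline (Statistical considerations). The standard deviation (SD) of change is not printed; the article says only: "A pooled standard deviation for change from baseline across T2 genes was derived from a historical bronchoscopy study". The correlation ρ between baseline and end of treatment is not given either. I assume a range of 0.3 to 0.9.

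**The plan's own figure.** Reading 0.72 as the full width:

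- √(1/32 + 1/16) = 0.3062
- SD of change = 0.72 / (2 × 1.96 × 0.3062) = 0.60
- Putting 0.60 back: 2 × 1.96 × 0.60 × 0.3062 = 0.72

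The stated width is thus coherent with N = 48 and an SD of 0.60. Because the SD was back-solved, this is not an independent reproduction. The width ratios below do not depend on the SD, on the log base, or on whether 0.72 is the full width or the half-width.

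**Effect of baseline adjustment.** With variance σ² at both visits:

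- variance for change = 2σ²(1 − ρ)
- variance for ANCOVA = σ²(1 − ρ²)
- ratio of standard errors = √((1 + ρ)/2)

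The adjusted width is 0.72 × √((1 + ρ)/2). The number needed for the same 0.72 width is 48 × (1 + ρ)/2.

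| ρ (assumed) | Width ratio | Adjusted width | Narrower by | N for width 0.72 |
|---|---|---|---|---|
| 0.3 | 0.806 | 0.58 | 19% | 31.2 |
| 0.5 | 0.866 | 0.62 | 13% | 36.0 |
| 0.7 | 0.922 | 0.66 | 8% | 40.8 |
| 0.8 | 0.949 | 0.68 | 5% | 43.2 |
| 0.9 | 0.975 | 0.70 | 3% | 45.6 |

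With t quantiles and a small-sample allowance for the estimated coefficient, the change-score width is 0.74. The ANCOVA widths are 0.60, 0.65, 0.69, 0.71 and 0.73. The gain shrinks but keeps its direction.

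**Simulation.** 4,000 trials per ρ, Gaussian log values, 16 against 32, change SD 0.60 and no treatment effect. Widths for change and ANCOVA were 0.726 and 0.588 (ρ = 0.3), 0.725 and 0.638 (0.5), and 0.714 and 0.666 (0.7). Every mean estimate lay within 0.005 of zero, so both estimators are unbiased over randomisation.

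**Chance imbalance.** The baseline mean difference has SD 0.306σ, so an imbalance beyond 0.5σ has a probability of about 10% per gene, before any benefit from FeNO stratification. With σ = 0.60/√(2(1 − ρ)), an imbalance of 0.5σ shifts the change contrast by (1 − ρ) × 0.5σ: 0.18, 0.15, 0.12, 0.09 and 0.07 for the five values of ρ. For scale, the 20% change that the article treats as minimally interesting is ln 1.2 = 0.18 if the scale is natural log.

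This shift is not a second cost on top of the wider interval. Since 2(1 − ρ) = (1 − ρ²) + (1 − ρ)², the last term is the imbalance contribution, and the change-score interval already contains it.

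**The case against.** The case for leaving the plan as it is has several parts.

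- **The plan is consistent with itself.** It is sized on change, analysed on change, and accepts a width of 0.72. A reader might infer that the primary analysis misses its precision target. It does not, because the target was set on the unadjusted contrast. This stands.
- **The gene model is not a simple change score.** It is a paired negative-binomial model for counts, in which the baseline count is part of the response. An ANCOVA term does not carry over directly, and the variance formulas are only approximate there. Different data types also plausibly explain the different models. This stands for single genes but not for GSVA and singscore values, which are continuous.
- **The estimator is not biased.** A reader might infer from the imbalance figures that the result is biased. Pairing removes each participant's own level, and the contrast is unbiased over randomisation; the shift is conditional on an imbalance that the interval already allows for. This stands.
- **FeNO stratification helps.** The Discussion reports that FeNO correlates with T2 gene expression and inversely with T17 expression, so imbalance may be smaller for those genes. The article claims no such link for the IL-6 trans-signalling, Th1 or JAK1-related genes. This stands in part.
- **The article is condensed.** Pairing could be implemented in more than one way, and the full protocol or SAP may give the exact model terms. That limits confidence. Even so, the article lists the terms of both models in the same section and names baseline only for the secondary one.

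**Conclusion.** The point holds as a modest efficiency gain. As published, the primary analysis contrasts changes between arms with no baseline-expression term named, while the secondary endpoints adjust for baseline. Adjustment would bring the width of 0.72 down to between about 0.58 (ρ = 0.3) and 0.70 (ρ = 0.9), that is, 19% to 3% narrower. This rests on an assumed ρ and on equal variances on the log scale, and it is approximate for count data. If ρ is 0.8 or above, the gain is 5% or less.

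Two further inferences are not supported. One is that 48 participants are too many: the numbers in the last column of the table depend wholly on a ρ that the article does not give. The other is that the paired negative-binomial model should be replaced: a gain on Gaussian log values has not been shown to transfer to that model, and fitting a separate baseline covariate for every gene is a debatable trade-off.

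**What to change.** Before database lock:

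1. Analyse change in the GSVA and singscore values by ANCOVA, with the baseline score and study drug as covariates, matching the secondary endpoints.
2. Keep the paired negative-binomial model as the main analysis of individual genes, and state how baseline enters it.
3. Pre-specify, as supportive, a baseline-adjusted analysis of log-scale expression for the pre-defined gene list.

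The cost is a few sentences in the analysis plan and a further set of fits over a fixed list of genes. No new samples or visits are needed.
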